4.1.2. Study phases

The number of visits is equal in the two groups. See flowcharts 1 and 2 and Figures 1 and 2 on the following pages.

The study consists of 4 phases, the contents of which are described in detail in the following.

4.1.3. Medication start phase**:** week 0 (7 days)

*Groups A and B*

After the patient has signed the informed consent form, an agreement concerning overnight stay is made with an in-patient ward in one of the county's psychiatric wards. When this has been decided, the patient can be included in the study and randomised to group A or B. All patients are switched from their present antidepressant treatment to duloxetine 60 mg daily in the morning. Patients who do not receive any current pharmacological treatment will also receive duloxetine 60 mg daily. Patient data are collected by means of questionnaires and forms as shown in flowchart 1 under inclusion visit. A deviation of +/- 2 days (window) of the duration of this phase due to a possible acute shortage of beds in the in-patient ward is acceptable.

Group B

At inclusion this group is also elucidated idiographically in regard to depression symptoms.

4.1.4. Hospitalisation phase: week 1 (7 days)

All study participants are hospitalised and meetings with the study investigators are envisaged for each working day. All patients (both groups, A and B) are hospitalised in an open in-patient ward. See Figures 1 and 2. Previously hospitalised patients can be discharged if their condition permits it. Patients admitted due to study participation will be discharged 6 days after admission unless their condition does not allow it. If the patient stays in hospital the trial will follow the usual guidelines, but the visits will take place in the in-patient ward whenever necessary.

Group A

- During hospitalisation, Group A patients go through 3 sleep deprivations, the first one on the day of admission (see Figure 2). Sleep deprivation is mainly carried out as total sleep deprivation, i.e. the patients stay awake all night. However, in some cases partial sleep deprivation may be used, in which the patient is woken up at 02.00 a.m. and has to stay awake for the remains of the night. This can be done either due to an individual patient evaluation made by the investigator or due to a wish on the part of the patient. There may be good reason for using partial sleep deprivation in case of medical diseases such as diabetes, where the blood sugar level can get out of balance, or in other diseases that may be influenced by a longer wake period. Also elderly patients expect not to be able to stay awake all night may also profit from partial sleep deprivation. Patients who experience that their first and total sleep deprivation is too demanding may also switch over to partial sleep deprivation. A combination of total and partial sleep deprivation is thus permitted.
- In the evening after each sleep deprivation the patients must go to bed at 9 p.m. at the very latest and get up at 7 a.m. the following morning (sleep-phase advance).
- The treatment with duloxetine continues unchanged, with a dose of 60 mg daily.
- The patients are informed about light treatment on the day of admission which is given for the first time the following morning and subsequently each day of the study period. The duration of light treatment is 30 minutes. The time of day of the light treatment is decided after completion of the MEQ questionnaire (see psychometrics paragraph). In addition to this, to fight tiredness, the patients take light treatment at 4 a.m. each night during the period of sleep deprivation.
- At each visit, the patients are taught how to maintain their diurnal rhythm after discharge by an approximate bed time at 11 p.m. and a getting-up time at 8 a.m. the very latest. The patients receive instructions about the use of the medication and sleep diaries.
- Apart from exercise, the patients are allowed to join all milieu-therapeutic activities in the ward.

Group B

- In one of the first few days after admission, Group B patients are instructed by a physiotherapist in an individually designed exercise programme. A plan for follow-up meetings with the physiotherapist is agreed upon. The number of follow-up meetings is the same as the number of visits to the study clinicians who assess treatment effect, and if possible all planned visits during the study will be scheduled together. The patients are allowed to join all milieu-therapeutic activities in the ward.
- Duloxetine treatment continues unchanged, with a dose of 60 mg daily.
- During the first 24 hours in the hospital the patients collect 24-hour urine for the measurement of cortisol. On their second day the patients give saliva samples in the morning for the measurement of cortisol.

4.1.5. Follow-up period I: week 2 until week 9 (included) (7 weeks)

During this phase the patients are examined weekly.

Group A

- Patients with scores of 8 or more on the Hamilton Depression Scale at visit 4, 5 or 6 will be offered two additional – either total or partial - sleep deprivations in the week of their visit. If practical reasons prevent this, the two sleep deprivations can be performed in the following week. Both sleep deprivations must be performed during the same week (preferably Tuesday and Thursday). The patients should be admitted in the evening, preferably Tuesday for the first and Thursday for the second sleep deprivation. The patients stay awake during the night in the ward and can be discharged next morning. No further sleep deprivations are permitted during the remaining study period and they are not allowed to carry out sleep deprivation on their own at home at any time.
- Duloxetine treatment is continued with an unchanged daily dose of 60 mg.
- Light treatment at home is continued, with daily treatments as in the previous study phase. The patients can borrow the lamp from the hospital.
- Patient education concerning maintenance of diurnal rhythm is on a continuous basis, at each visit, with an envisaged bedtime at 11 PM and a wake-up time at 8 AM at the very latest.
- The patients are instructed on a continuous basis how to fill in medication diary, light diary and sleep diary.

Group B

- Duloxetine treatment is continued with an unchanged daily dose of 60 mg.
- The patients receive weekly instructions and training within their individual exercise program. The time at which the patients have to show up should as far as possible be coordinated with the other visits to the hospital.

4.1.7. Discussion of design

The choice of a single-blinded trial was the best choice of design, as it is not possible to blind the study towards the patients. To secure placebo response in both groups, this design was chosen to encourage the same expectations as to effect of treatment in both treatment groups. In both treatment groups the used methods aim at a change or stabilisation of diurnal rhythm. Exercise as well as sleep deprivation function as "zeitgebers" (time givers ). We thus look at two different chronotherapeutic interventions. It can be expected that sleep deprivation will have an immediate effect, while the effect of exercise is seen only after a certain period of time. In follow-up phase I, group B will thus function as a control group, while follow-up phase II will be a comparison of two different methods.

Exercise has also been chosen, because it is a very well-accepted treatment which in the same way as light treatment and sleep deprivation makes it possible for the patients to make an effort to improve their own condition. The individual adaptation of the exercise programme ensures that the demands are not too high and thereby act a demotivation. An idiographic examination is only made in group B. The reason for this is to ensure an even weighting of expectations from the two groups. Cortisol measurements in saliva and urine are made during hospitalisation and only in group B patients in order not to overstretch sleep deprivation patients. The medication start period has been chosen, so patients don't experience possible new side effects and exercise/sleep deprivation at the same time. It is also an advantage that duloxetine has reached a steady state concentration in the body before the other interventions show an effect.

The steady state of duloxetine concentrations is also an advantage in relation to the effects of the other interventions.

Group A is flexible as to number of sleep deprivations, with the possibility of administering two additional sleep deprivations in weeks 4, 5 or 6. This is to give patients with severe depression a better chance of remission without inconveniencing patients with less severe depressions to no avail.

The choice between total and partial sleep deprivation has been introduced to be able to adjust the strain to the patients' condition. By this measure we take a step towards clinical reality, to which we aim to generalise the results of the study.

| **Study period and duration** | **Medication start phase:**  **7 days** | **Hospitalisation:**  **7 days**  Visits on week days | **Follow-up phase I:**  **7 weeks**  **Visits each week** | | | | | | | |
| --- | --- | --- | --- | --- | --- | --- | --- | --- | --- | --- |
| **Week no.** | **0** | **1** | **2** | **3** | **4** | **5** | **6** | **7** | **8** | **9** |
| **Visit no.** | **1 (Inclusion)** | **2** | **3** | **4** | **5** | **6** | **7** | **8** | **9** | **10** |
| **M.I.N.I.+ SCID I and II**  **SPAQ + MEQ + DIAD + SPS** | x |  |  |  |  |  |  |  |  |  |
| **Hamilton + MES + MAS + MDI + UKU + WHO-5** | x | x | x | x | x | x | x | x | x | x |
| **Preskorn** | daily | daily | daily | daily | daily | daily | daily | daily | daily | daily |
| **Borg scale + external assessment (exercise)** |  | x | x | x | x | x | x | x | x | x |
| **SCL-92** | x | x | x | x | x | x | x | x | x | x |
| **Idiographic method (gr. B)** | x | x | x | x | x | x | x | x | x | x |
| **EKG + Blood pressure + Blood samples** | x |  |  |  |  |  |  |  |  | x |
| **Collecting diurnal urine (gr. B)** |  | x |  |  |  |  |  |  |  |  |
| **Saliva samples (gr. B)** |  | x |  |  |  |  |  |  |  |  |
| **Sleep, light, medication and exercise diaries and status** | x | x | x | x | x | x | x | x | x | x |
| **Stanford Sleepiness Scale** |  | x |  |  |  |  |  |  |  |  |
| **Expectation to treatment** | x |  |  |  |  |  |  |  |  |  |
| **Evaluation of treatment** |  |  | x |  |  |  |  |  |  | x |
| **TEMPS-A** |  |  |  |  |  |  |  |  |  |  |

**Flowchart 1(week 0 to 9, duration 9 weeks**)

| **Study period and duration** | **Follow-up phase II:**  **20 weeks**  **Visit every 4th week** | | | | | |
| --- | --- | --- | --- | --- | --- | --- |
| **Week no.** | **9*** | **13** | **17** | **21** | **25** | **29** |
| **Visit no.** | **10** | **11** | **12** | **13** | **14** | **15** |
| **M.I.N.I.+ SCID I and II**  **SPAQ + MEQ + DIAD + SPS** |  |  |  |  |  |  |
| **Hamilton + MES + MAS + MDI + UKU + WHO-5** | x | x | x | x | x | x |
| **Preskorn** | weekly | weekly | weekly | weekly | weekly | weekly |
| **Borg scale + external assessment (exercise)** | x | x | x | x | x | x |
| **SCL-92** | x | x | x | x | x | x |
| **Idiographic method (gr. B)** | x |  |  |  |  | x |
| **EKG + Blood pressure + Blood samples** | x |  |  |  |  | x |
| **Collecting diurnal urine (gr. B)** | x |  |  |  |  | x |
| **Saliva samples (gr. B)** |  |  |  |  |  |  |
| **Sleep, light, medication and exercise diaries and status** | x | x | x | x | x | x |
| **Stanford Sleepiness Scale** |  |  |  |  |  |  |
| **Expectation to treatment** |  |  |  |  |  |  |
| **Evaluation of treatment** | x |  |  |  |  | x |
| **TEMPS-A** |  |  |  |  |  | x |
| **WHO-Five** | x | x | x | x | x | x |

**Flowchart 2 (week 9 to 29, duration 20 weeks)**

***Week 9 is a repetition of flowchart 1 to clarify the trial phases**

**Figure 1. Duration of treatment phases and the attached treatment elements**

| **Day visit** | **Hospitalisation** | **Day visit** | **Day visit** |
| --- | --- | --- | --- |
| **Duloxetine start** | **Sleep deprivation + light + sleep-phase-advance / exercise** | **Diurnal rhythm + light+ additional sleep deprivations in week 4, 5 or 6 / exercise** | **Diurnal rhythm + light/ exercise** |

| **Medication start phase** | **Hospitalisation phase** | **Follow-up phase I** | **Follow-up phase II** |
| --- | --- | --- | --- |
| **1 week** | **1 week** | **7 weeks** | **20 weeks** |

**Figure 2. Example of the course of sleep deprivation and sleep-phase-advance (SPA) with admission on a Monday and discharge on a Saturday.**

| **Sleep deprivation I** | **SPA I** | **Sleep deprivation II** | **SPA II** | **Sleep deprivation III** | **SPA III** |
| --- | --- | --- | --- | --- | --- |

| **Admission** |  |  |  |  | **Discharge** |  |
| --- | --- | --- | --- | --- | --- | --- |

| **Monday** | **Tuesday** | **Wednesday** | **Thursday** | **Friday** | **Saturday** | **Sunday** |
| --- | --- | --- | --- | --- | --- | --- |

**4.2. Psychometrics**

To make a diagnosis, to examine co-morbidity and possible exclusion diagnoses the M.I.N.I. (Mini International Neuropsychiatric Interview) (Sheehan et al. 1998) and the SCID (First, 2002) will used, both based on the American DSM-IV diagnostic system (APA 1994). DSM-IV also contains the ”Seasonal Pattern Specifier” we use for the diagnosis of winter depression (”Seasonal Affective Disorder”). To elucidate atypical depression, the DIAD (Diagnostic Interview for Atypical Depression) (Terman et al 2003) is used.

Patients with personality disorders are identified and excluded by means of the SCID (First, 2002). DSM-IV subclassifies major depression into ”Major depressive disorder, single episode” (296.2) and ”Major depressive disorder, recurrent” (296.3). Bipolar disorder is first classified by using the M.I.N.I. criteria for ”previous hypomanic/manic episode”, and patients fulfilling the diagnostic criteria for previous manic or hypomanic episode are then subdivided according to DSM-IV into the diagnostic codes ”Bipolar I disorder, most recent episode depressed” (296.5), ”Bipolar I disorder, most recent episode unspecified” (296.7), and "Bipolar II disorder" (296.89).

For the assessment of severity of depression clinician-rated as well as self-rating scales are used.

The clinician-rated scales are the 17-item Hamilton Depression Scale (HAM-D17),(Bech et al. 1986), the Melancholia Scale (MES) (Bech 2002a), and a Hamilton Depression 6-item subscale (HAM-D6), (O'Sullivan et al. 1997, Licht et al. 2005). Sleep studies usually use the HAM-D6, as it has no sleep item. During hospitalisation, the patients are assessed daily with the HAM-D6. During hospitalisation, patient assessments are made daily with HAM-D6. A minimum score of 13 on the 17-item Hamilton Depression Scale has been chosen for inclusion, as some patients with long term depressions have scores on this moderate level, which, however, has a marked impact on social functioning and quality of life. This is owing to the peripheral depression symptoms which still are present. Another reason is that one single measurement may be unreliable in patients with great day-to-day variability of the degree of depression. It has also been demonstrated that the effect of antidepressant treatment starts at this level (Paykel 1990).

The self-rating scales used are the SCL-92 (Symptom Checklist) (Olsen et al 2004) and the Major Depression Inventory (MDI) (Bech et al. 2001, Olsen et al. 2003), - the MDI, however, in a modified version in which severity as well as frequency of the depression symptoms are assessed .

To subjectively assess the day-to-day and time of day variability of the degree of depression, the Preskorn scale will be used daily at 9 and 12 a.m. and 3, 6 and 9 p.m., and at awakening and bedtime during the first week prior to hospitalisation. It will be examined whether variability of degree of depression and diurnal variation are predictors of response to sleep deprivation. During the first 9 weeks of the study, the Preskorn questionnaire will also be used for daily measurements of degree of depression, and subsequently once weekly until week 29.

A questionnaire has been developed for the patient's assessment of his/her expectation to treatment, and thus an evaluation of an even distribution of the placebo effect among the two treatment groups. It is filled in at inclusion, after the patient has received detailed information about the project.

The WHO-Five Well-being Index (WHO-5) will be used at each visit to assess quality of life. This instrument contains 5 questions and has been validated in a number of studies (Bech 2004).

Specific questionnaires have been developed to capture the patient's impression of the treatment after 2 weeks (i.e. immediately after discharge), also offering the possibility of open statements. After 9 and 29 weeks, the patients are asked for repeated assessments of their treatment.

The patient's temperament is assessed by the TEMPS-A at the end of the study, in week 29 (Akiskal et al. 2002). This questionnaire contains five scales examining personality traits that have been present throughout the patients' lives (character traits). The five traits are: depressiveness ("depressive"), anxiousness ("anxiety"), irritability ("irritable"), mood swings ("cyclothymia") and extraversion, energeticness ("hyperthymia"). The reason for using this scale at the end of the study is that the depressive condition, which expectedly is less marked at the end of the study, at an earlier stage would affect the self-assessment of the person and thus rather reflect the current condition than character traits.

To decide at which hour light treatment should be administered, the Morningness-Eveningness Questionnaire (MEQ) will be used (Horne et al. 1976, Horne et al. 1977, Terman et al 2005).

Side effects will be rated by means of the UKU (Udvalget for Kliniske Undersøgelser, evaluation form for side effects) (Lingjærde et al. 1987), with relevant questions concerning serotonergic and noradrenergic side effects.

The Mania Scale (MAS) is to be used at all visits to assess the possible development of a hypomanic or manic condition. A MAS score of 15 or more thus means exclusion from the study.

The SPAQ (Seasonal Pattern Assessment Questionnaire) (Kasper et al 1989) questionnaire will be used to assess seasonal variability of the depression.

The idiographic method is to be used at all visits, but only in group B patients. The method implies free constructs by the patients who describe the symptoms they have experienced in connection with their current depressive episode. At each visit, the free construct is given as a percentage value in relation to the baseline construct (set 100% for each construct at baseline, e.g. how much of 100% tiredness is your tiredness today?), thus measuring change from inclusion an onwards. In contrast to the other scales used in the study, this method is not an absolute measure of severity. With this method we hope to obtain a more balanced picture of the symptoms we obtain by standardised methods such as questionnaires and rating scales, and we also hope to accomplish a greater degree of sensitivity towards change in the condition. The strength of this method is that symptoms which patients have experienced during their depression are not forced into the standardised boundaries of a rating scale or a questionnaire. The method is based on Kelly's ideas on free constructs (Kelly, 1955). It has been used in GRID-QOL (Thunedborg et al 1995), a computer-assisted quality of life rating system.

At inclusion, sleep and exercise are evaluated for both groups. Sleep diaries, exercise diaries and medication diaries are completed in both groups at each visit. Light diaries are only completed in group A.

The scales are employed as indicated in flowcharts 1 and 2. Flowchart 1 covers the first 9 weeks while flowchart 2 covers weeks 10 to 29.

**4.3. Efficacy parameters**

4.3.1 The primary efficacy parameter is the number of patients in the two group that have achieved response to treatment or remission after 2, 9 or 29 weeks. Response is defined as a more than 50% reduction in HAM-D17 scores after inclusion into the study while remission is defined as a score of 7 or less on the HAM-D17.

4.3.2. Secondary effect parameter is the number of those patients in the two treatment groups who have experienced long-lasting response or remission after 9 weeks and after 29 weeks. Lasting response is defined as patients responding after 2 weeks of enrolment in the study and the response either lasting until week 9 (early lasting response) or until week 29 (episode response). Lasting remission is defined as being in remission after 2 weeks in the study and the remission either lasting until week 9 (early lasting remission) or until week 29 (episode remission). Response and remission are defined as mentioned under primary efficacy parameter. Patients who according to the protocol receive further sleep deprivations in week 4, 5, or 6 thus are cannot be defined as being in early, lasting remission. Response and emission are defined as mentioned under primary efficacy parameter. Patients who according to the protocol carry out additional sleep deprivation in weeks 4, 5 or 6 thus are defined not to be in early lasting remission.

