**3. OBJECTIVE**

The main objective of the trials is to examine whether sleep deprivation in combination with light treatment, duloxetine and maintenance of diurnal rhythm (Group A) is able to induce a faster onset of action and lasting antidepressive response compared to an individually designed exercise programme in combination with treatment with duloxetine (Group B).

Secondary objectives are studies of cortisol concentration, variability of the degree of depression, the idiographic method and finally, applicability and effect of exercise over 9 weeks under supervision. The following hypotheses ar going to be tested in the study:

- Is sleep deprivation in combination with duloxetine, light and maintenance of diurnal rhythm (Group A) able to induce a greater degree of response or remission than exercise in combination with duloxetine (Group B). The hypothesis is tested after 2, 9 and 29 weeks of therapy?
- Is it possible for patients with major depression during the supervised course of treatment of 9 weeks to achieve the National Health Board's recommendation of exercising 30 minutes per day, and is there any association between the exercise effort and the degree of depression after 29 weeks?
- Is the cortisol concentration as measured in urine and saliva the beginning of week 2 correlated to the severity of depression as measured after 2, 9 and 29 weeks of therapy?
- Is the concentration of cortisol measured in saliva correlated with the concentration of cortisol in diurnal urine?
- Is the idiographic method more sensitive to change of degree of depression than clinician- and patient-rated scales and questionnaires for depression?
- Can variability in the degree of depression as measured with the Preskorn scale (see psychometrics) predict response to sleep deprivation?

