**11. STATISTICS**

To analyse the number of patients with response or remission at three defined points in time (weeks 2, 9 and 29), Chi2 distribution is used. To do this, the Last Observation Carried Forward (LOCF) is employed. The assessment of the longitudinal courses of response and remission (and sustained response and remission) uses survival analysis (Kaplan-Meier survival-analysis) including log-rank test to calculate p values (Stassen et al 1993). Furthermore, the Mixed Model Repeated Measures (MMRM) (Brown et al. 1999) will analyse readily available depression scores to determine the difference between the two groups. Thus, MMRM does not use LOCF. The association between cortisol and depression scores and the association between urine and saliva cortisol has been calculated by means of the Spearman correlation coefficient *rho*. The same statistical method will be used to test the association between the various degrees of depression and the effect of sleep deprivation. The idiographic method will be analysed by means of MMRM. Exercise will be analysed as the percentage of compliance to the predefined goal (30 minutes exercise daily). Moreover, the achieved amount of exercise (combined score of the Borg scale and the amount of performed exercise) will be graded into light/moderate/intensive in follow-up phase I. It will be compared with the degree of response and remission in week 29 and analysed by Chi2 distribution. The number of study subjects has been calculated on the basis of an expected depression score of 24 on the 17-item Hamilton Depression Scale at inclusion into the study for both groups. After 9 weeks of treatment a decrease to 10 in group A and to 13 in group B is expected. The expected standard deviation is 4. With a type-I error of 0.05 and 0.90 power, 39 patients are required for each group.

No interim analyses have been planned.

GCP guidelines permit that patients may be excluded from the data analysis after the end of the study, if eligibility violations have taken place and if this was not known during the project. This may refer patients who have fulfilled the inclusion criteria, but have not taken any of the study medication, or have taken other prescriptions without telling the investigator, and where these violations were not known until the end of the study. All other patients assessed at the time of inclusion in the study are included in the statistical analyses according to the intention-to-treat method.

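### Section 4.3.1 makes response or remission at weeks 2, 9 or 29 primary with no lead test; if each is tested at 0.05 and any one counts as success, the false-positive risk is about 12–16% (three tests) or 19–26% (six) with an uncorrected chi-square

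*Protocol*

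**What the plan says.** - Section 4.3.1 sets the primary parameter as "response to treatment or remission after 2, 9 or 29 weeks". Response (HAM-D17 down by more than half) and remission (HAM-D17 of 7 or less) are defined separately.
- Section 3, on the main comparison of groups A and B: "The hypothesis is tested after 2, 9 and 29 weeks of therapy".
- Section 11: "To analyse the number of patients with response or remission at three defined points in time (weeks 2, 9 and 29), Chi2 distribution is used". For these tests "the Last Observation Carried Forward (LOCF) is employed". The version of the chi-square test is not given.
- Section 11, on sample size: "With a type-I error of 0.05 and 0.90 power, 39 patients are required for each group". This follows from an "expected depression score of 24 on the 17-item Hamilton Depression Scale at inclusion" and the sentence "After 9 weeks of treatment a decrease to 10 in group A and to 13 in group B is expected", with a standard deviation of 4.
- Section 12 raises the planned enrolment to 50 per group. Section 11 plans no interim analyses.

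None of these places ranks the time points, ranks response against remission, or says whether one significant result is enough.

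**The concern.** The primary definition is a list joined by the word *or*, in outcome and in time. Read as a composite it holds three tests; read as two outcomes it holds six. The protocol does not say which result decides the trial.

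This matters in two ways.

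- **Interpretation.** The time points answer different questions. Section 3 asks about both the speed and the durability of the effect. Section 4.1.7 treats group B as a control during follow-up phase I, but treats phase II as a comparison of two methods. A difference only at week 2 and a difference only at week 29 would support different conclusions, yet either could be reported as the primary result.
- **Error rate.** If any one of several tests at 0.05 may carry the claim, the chance of at least one false positive exceeds 0.05.

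**Working it through.** **1. The plan's own figure.** Difference 13 − 10 = 3, SD 4, two-sided 0.05, power 0.90:

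n = 2 × (1.960 + 1.282)² × 4² / 3² = 37.4, so 38 per group. The t-test version gives 38.3, so 39.

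The stated 39 is reproduced. It belongs to one comparison of mean scores at week 9, not to a comparison of response or remission rates.

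**2. Independent tests at 0.05.**

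- Three tests: 1 − 0.95³ = 14.3%
- Six tests: 1 − 0.95⁶ = 26.5%

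Tests on the same patients are correlated, and LOCF adds to this by copying earlier values forward. Both pull the figure down, towards 5% if all tests were perfectly dependent.

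**3. Simulation with no true difference.** Inputs from the protocol: mean baseline 24, inclusion at 13 or more (section 4.6.3), the definitions of response and remission, 39 or 50 per group, and LOCF. The week-9 mean of 11.5 is the midpoint of 10 and 13. Assumed: means of 15 at week 2 and 10 at week 29, baseline SD 4, follow-up SD 6, correlation 0.3 between baseline and follow-up, equal correlation between follow-up weeks, and half of the dropout before week 9. There were 20,000 trials per setting, with each test at 0.05. Chance of at least one significant result:

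| Per group | Correlation between weeks | Dropout by week 29 | Uncorrected, 3 tests | Uncorrected, 6 tests | Corrected, 3 tests | Corrected, 6 tests |
|---|---|---|---|---|---|---|
| 50 | 0.3 | 0% | 14.8% | 24.9% | 9.1% | 14.9% |
| 50 | 0.3 | 40% | 14.6% | 24.4% | 9.1% | 14.6% |
| 50 | 0.85 | 0% | 12.3% | 20.8% | 8.4% | 12.7% |
| 50 | 0.85 | 40% | 12.1% | 20.2% | 8.0% | 12.4% |
| 39 | 0.3 | 0% | 14.5% | 25.3% | 8.0% | 13.1% |
| 39 | 0.3 | 40% | 14.0% | 24.4% | 7.9% | 12.8% |
| 39 | 0.85 | 0% | 13.0% | 22.1% | 7.3% | 11.3% |
| 39 | 0.85 | 40% | 11.8% | 20.5% | 7.2% | 11.1% |

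The three-test columns use the composite. With SD 4 throughout, no dropout and an uncorrected test, raising the correlation from 0 to 0.9 moves the three response tests from 15.3% to 12.9% and all six from 25.4% to 20.3% at 50 per group. At 39 per group the six tests fall to 19.5%. Values slightly above 14.3% for three tests arise because a single uncorrected chi-square can itself reject a little more than 5% of the time (up to 5.8% in these runs).

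Over all settings examined, the uncorrected test gives about 12–16% and 19–26%. The corrected test gives about 7–10% and 10–14%, with a few settings at the wider SD reaching 15%.

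**4. Composite against response.** Remission without response needs a score of 7 or less that is not below half the baseline, so a baseline of at most 14. With inclusion at 13 or more, only a patient who starts at 13 or 14 and scores exactly 7 qualifies. The composite is therefore almost the same outcome as response.

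**5. What adjustment would cost.** Take baseline as 24, so response means a score below 12, with normal scores and SD 4 at week 9:

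- Group A: Φ((12 − 10)/4) = Φ(0.50) = 0.69
- Group B: Φ((12 − 13)/4) = Φ(−0.25) = 0.40

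At 50 per group, exact power for this comparison is about 0.85 at 0.05 and 0.61 at 0.05/6. Splitting alpha over six tests is expensive; ordering the tests leaves the first at full alpha.

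**The case against.** Four objections deserve weight.

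- **The alpha is inferred.** A reader might conclude that the protocol tests every primary comparison at 0.05 and claims 5% overall. It says neither. The 0.05 is attached to a mean-score sample size, and no sentence says that one significant test suffices. This stands, so the inflation must be stated as conditional on those two readings.
- **An analysis plan may settle it.** Order and adjustment are often set there, and that document is not at hand, so their absence alone is no fault. But the identity of the primary endpoint is protocol content. Section 4.3.1 does fix it, as an open list, and a later plan that picked one entry would be replacing the definition.
- **The size is uncertain.** A reader might take the 14% for three independent tests as a minimum. It is not: correlation and LOCF bring it to about 12%, and a continuity correction, which the protocol neither requires nor rules out, to 7–10%. This stands as to size, but no setting examined came down to 5%.
- **Week 9 is not the only candidate.** The sample size uses week 9, but for a mean score, and the main objective includes speed of onset, which could favour week 2. This stands. The choice belongs to the sponsor; the need to choose does not go away.

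**Conclusion.** The point holds in conditional form. The protocol gives equal primary standing to three time points and leaves open whether response and remission are one outcome or two.

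If each test uses 0.05 and any one significant result counts as success, the overall false-positive risk with an uncorrected chi-square is roughly 2.4 to 3.2 times 5% for three tests (12–16%) and 3.8 to 5.2 times for six (19–26%). With a continuity correction it is roughly 1.4 to 2 times (7–10%) and 2 to 3 times (10–14%, at most 15%).

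The direction is firm. The exact figures rest on assumed week means, standard deviations, correlations and dropout. The documents do not support saying that the trial has a known error rate of some given percentage in place of a promised 5%.

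**What to change.** In sections 4.3.1 and 11, and to match in the first hypothesis of section 3, name one outcome at one time point as the single primary test, before any outcome data are seen. One workable choice is response at week 9, the time point on which the sample size is built. If speed of onset is the main question, the sponsor may put week 2 first.

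Then list the remaining tests in a fixed order, each at 0.05 and each done only if the one before it is significant. For example: response at week 9, week 2, week 29, then remission in the same order. Report everything after the first non-significant result as descriptive. State the version of the chi-square test. Because a false claim under no difference then requires the first test to reject, the overall error is that of a single test.

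The change needs wording only, with no extra patients or visits. The price is that an early failure makes later results descriptive, including any real difference at a later place in the order. If response at week 9 leads, its power should be stated as well (about 0.85 at 50 per group under the assumptions above), since the figure of 39 was derived for mean scores.
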